## Abstract

Primary progressive aphasia (PPA) is a neurological syndrome characterized by the gradual deterioration of language capabilities. Due to its neurodegenerative nature, PPA is marked by a continuous decline, necessitating ongoing and adaptive therapeutic interventions. Recent studies have demonstrated that behavioral therapies, particularly when combined with neuromodulation techniques such as transcranial direct current stimulation (tDCS), can improve treatment outcomes, including the long-term maintenance and generalization of therapeutic effects. However, there has yet to be a phase II multisite study examining the efficacy of tDCS in individuals with PPA. This paper reports the methods and analyses for the clinical trial NCT05386394. A total of 120 adults with non-fluent and logopenic variant PPA will receive a novel spoken Naming and Spelling (NaSp), individuals with semantic variant PPA will be excluded from this trial. Participants will receive NASP therapy over two periods of 3 weeks (Monday through Friday, for a total of 15 non-consecutive days) combined with anodal (a-tDCS) and sham tDCS (s-tDCS). They will be randomly allocated to receive a-tDCS either during the first or second intervention period. The study will be conducted at four sites across the United States and Canada. Outcome measures will be recorded immediately before and after each intervention period, as well as 3 months after each period. Primary outcome measures will be the change in phonemic accuracy in spoken picture naming and letter accuracy in spelling for trained nouns and verbs. Changes from the a-tDCS and s-tDCS periods will be compared to determine the efficacy of tDCS. Primary outcomes will be analyzed using statistical methods that account for repeated measures within participants (namely generalized estimating equations). A significant adjuvant effect of tDCS will be determined if differences in phonemic accuracy and/or letter accuracy immediately following a-tDCS intervention and/or at the 3-month follow-up are greater (at p < 0.05) than those of the s-tDCS intervention. This trial is the first multisite, fully powered, randomized, double-blind, sham-controlled, crossover study of the effectiveness of tDCS as an adjuvant to behavioral treatment for spoken naming and spelling deficits in individuals with PPA. Specific challenges in designing the protocol are considered.

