### Sample size

Based on the crossover design, we calculated that 120 participants with PPA (40 at each of the three sites) are needed to achieve 85% power in detecting the target effect size (e.s.^target^). The power of the design to detect e.s.^target^ using an estimator is calculated as/is Φ(*e.s*_*target*_/√(*rate*_*design*_/*n*) - 1.96), where *rate*_*design*_/*n* represents the standard error squared of the estimator, and Φ is the cumulative distribution of the normal. Plausible values of *rate*_*design*_ and effect sizes are determined based on similar outcomes from previous studies with comparable crossover designs. The estimated 15% dropout rate is based on previous studies involving individuals with PPA undergoing tDCS and language therapy. In prior RCT from members of our team, attrition was ~15% during the first phase, mostly due to unrelated medical issues (Tsapkini et al., 2018). This rate was used to estimate the required sample size.

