#### Primary outcome measures

The primary outcome measure will be the change in performance between time points, as measured by phonemic accuracy (during spoken naming) and letter accuracy (during spelling) of trained items. Phonemic and letter accuracy will be calculated on a scale of 0–100%, with a higher number reflecting higher accuracy, using the Phonology analysis and Spelling analysis tools in Open Brain AI (Themistocleous, 2023).

At each assessment time point, participants undergo a comprehensive evaluation that includes the NaSp spoken naming and spelling task, which serves as the primary outcome measure. The task consists of 80 stimuli corresponding to the Level 1 stimuli previously outlined in the Therapy Stimuli section (along with 80 items included in Level 2 for identified participants). Accuracy on trained items is then computed separately.

The assessor presents all the words in the list. For each noun, participants attempt to name the item orally and then write their answer. No feedback is given, as some items serve as generalization items for either P1 or P2. After assessing the nouns, the same procedure is applied to the verbs.

All spoken and written responses are recorded. Spoken responses will be transcribed manually using the International Phonetic Alphabet, and written responses are captured using a smart pen (Symphony Smartpen by Livescribe, n.d.) to ensure accurate data collection. Both the spoken and written responses will be typed into a scoring document.

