### Statistical analysis

This trial investigates whether combining tDCS targeting the left IFG with a tailored spoken naming and spelling therapy improves language abilities and communication in individuals with PPA, with expected benefits extending to untrained tasks and lasting up to 3 months. It also aims to identify predictors of treatment response.

The primary outcomes will be analyzed using a general crossover formulation that considers each follow-up time point, the effects of treatment (s-tDCS vs. a-tDCS), phase (P1 or P2), and their interaction. For each participant, the data will include the order of treatments (s-tDCS in phase 1 and a-tDCS in phase 2, or vice versa) and changes in accuracy from before to after each phase for phonemic accuracy (during spoken naming) and letter accuracy (during spelling) of trained items.

The general crossover analysis will estimate parameters such as intervention effects in each phase and the overall average intervention effect. Estimates of these effects, standard errors, and confidence intervals will be calculated using the generalized estimating equation (GEE) method with robust variance estimation to account for correlations among repeated outcomes across different time points and phases within an individual. *P*-values will be exact and derived by comparing the estimates to the distribution calculated by permuting the order of intervention assignment across patients.

To address potential carryover effects inherent in the within-subject crossover design, a period-by-treatment interaction term will be included in the GEE model. A significant interaction will indicate possible carryover. In this case, follow-up sensitivity analyses will be conducted such as restricting analyses to Period 1 only, to confirm whether the treatment effect is robust. Washout adequacy will also be examined based on baseline performance at each phase.

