To identify the predictors of differential effects of tDCS vs. sham on primary outcomes, we will separately analyze clinical (PPA variant, severity of impairments), neural (functional and structural), genetic, cognitive, and demographic (age, sex) factors, as well as lifelong language experience (e.g., bilingualism) factors. We will employ a model comparison approach, evaluating each predictor type based on effect size and cross-validated R-squared variance. By sequentially adding each predictor type, we will measure the variance contributed by each factor and establish a threshold for acceptable variance from each factor. To account for multiple comparisons across the range of predictors tested, we will apply False Discovery Rate (FDR) correction using the Benjamini-Hochberg procedure (Benjamini and Hochberg, 1995). This approach controls the expected proportion of false positives among the predictors identified as significant, ensuring a balanced trade-off between Type I error control and discovery potential in the context of exploratory modeling.

Using cross-validated, R-squared model selection minimizes the need for extensive adjustments for multiple comparisons. We will also assess the significance of the remaining factors by comparing them to the bootstrap distribution of sorted t-statistics under the null hypothesis that no factors predict the tDCS vs. sham effect. This final model will help us identify individuals who demonstrate a statistically significant difference between the effects of tDCS and sham treatment.

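### The printed success rule lets any one of four unadjusted comparisons make the trial positive, so its false-positive rate exceeds that of a single test

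*Protocol article*

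**What the plan says.** The Abstract of the protocol article states a single conclusion, opening with "A significant adjuvant effect of tDCS will be determined if", and gives its condition as "differences in phonemic accuracy and/or letter accuracy immediately following a-tDCS intervention and/or at the 3-month follow-up are greater (at p < 0.05" in the comparison with the sham period.

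The other relevant places are:

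- **Primary outcome measures** makes the change in "phonemic accuracy (during spoken naming) and letter accuracy (during spelling) of trained items" primary. Both accuracies have the same rank, and no time point is singled out.
- **Statistical analysis** describes a "general crossover formulation that considers each follow-up time point" and lists among its estimates "intervention effects in each phase and the overall average intervention effect". It does not say which estimate decides the trial. P-values come from permuting the treatment order across patients.
- **Statistical analysis**, on predictors of response: "To account for multiple comparisons across the range of predictors tested, we will apply False Discovery Rate (FDR) correction". No counterpart is given for the primary comparisons.
- **Sample size** says that 120 participants "are needed to achieve 85% power in detecting the target effect size". The formula has one effect size, one standard error and the critical value 1.96. No outcome or time point is attached to it.

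**The concern.** Read plainly, the Abstract's rule has four ways to succeed: phonemic accuracy or letter accuracy, each immediately after treatment or at 3 months. Each is tested at 0.05, and any one is enough. When several tests feed one claim without adjustment, the chance of a false claim exceeds that of each test. Permutation makes each p-value exact but does not correct for choosing among four.

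The article presents the trial as a step toward clinical use of tDCS. A positive verdict could rest on one comparison of four that crossed the line by chance, and the reader would see it reported at p < 0.05. The stated power is also calculated for one test, so it describes a different decision from the one the Abstract prints.

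**Working it through.** **Inputs from the article.** Two primary outcomes; two time points in the rule; threshold 0.05; power 85% with critical value 1.96; n = 120. **Assumed:** the correlations among the four test statistics, because the article gives none.

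**1. The plan's own figure.** The formula is power = Φ(e.s./SE − 1.96). The 85% cannot be reproduced, because the target effect size and the variance rate have no numbers. Solved backwards, 85% needs e.s./SE = 1.96 + 1.036 = 2.996. The 1.96 is the critical value of one unadjusted two-sided 0.05 test.

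**2. False positives if the four tests were independent.**

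- Any two-sided rejection: 1 − 0.95⁴ = 18.5%.
- Two-sided p, counting only results favouring active stimulation: 1 − 0.975⁴ = 9.6%.

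**3. False positives with correlation.** Four normal statistics were simulated under no effect (2 million draws). In rows giving separate outcome and time values, the correlation across both is their product.

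| Assumed correlation | Any two-sided rejection | Favours a-tDCS, two-sided p | One-sided tests at 0.05 |
|---|---|---|---|
| none | 18.5% | 9.6% | 18.6% |
| outcomes 0.3, times 0.5 | 16.9% | 8.5% | 15.9% |
| all 0.5 | 15.6% | 7.8% | 14.4% |
| outcomes 0.7, times 0.8 | 12.9% | 6.4% | 11.8% |
| all 0.8 | 11.4% | 5.7% | 10.6% |
| all 0.9 | 9.4% | 4.7% | 8.8% |

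The rates for a single test are 5%, 2.5% and 5% respectively. Every entry exceeds the rate for its column.

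**4. Power of the rule as printed.** If all four true effects equal the target (each statistic centred at 2.996), the chance that at least one exceeds 1.96 is 99.95% at correlation 0, 98% at 0.5 and 92% at 0.9.

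**5. Power if alpha is split.** These figures are for one named comparison.

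- At 0.05/4 = 0.0125 the critical value is 2.498: Φ(2.996 − 2.498) = 69%. Restoring 85% would take 120 × ((2.498 + 1.036)/2.996)² ≈ 167 participants.
- At 0.05/2 = 0.025 the critical value is 2.241: Φ(2.996 − 2.241) = 77%.

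A fixed order or a single primary comparison leaves the leading test at 1.96, so its 85% stands.

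**The case against.** **On size.** A reader might infer that the error rate is three times the stated level. That needs either rejections in favour of sham to be counted, although the rule requires active stimulation to do better, or one-sided tests at 0.05, which the 1.96 in the power formula argues against. With two-sided p-values and only favourable results counted, the rate is about three times an implied 2.5%, but only 1.3 to 1.9 times the printed 5%. High correlation is also credible. Each word is named and then written in the same task, and the immediate and 3-month changes share a baseline, so independence is a ceiling rather than an expectation. At a common correlation of 0.9 the favourable-only rate is 4.7%, below 5% though still nearly twice 2.5%. These points stand and limit the size of the finding.

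**On power.** A reader might also infer that the trial is underpowered. The article does not support that. If all four effects equal the target, the printed rule has more than 85% power. The falls to 69% and 77% arise only if alpha is split, and only for one named comparison.

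**On placement.** The rule appears in the Abstract, and a fuller analysis plan could hold a hierarchy or an adjustment. That is possible, and mere silence in a condensed article would not be a finding. Here, however, the article prints an explicit success rule. A different rule elsewhere would contradict it, and the two would have to be reconciled.

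**On phase.** A phase II trial may tolerate more error, but the article states 0.05 and should then have a rule that delivers it.

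**Conclusion.** The concern holds for the rule as printed. One conclusion can be reached by any of four unadjusted comparisons, and neither the outcome section nor the analysis section names the one that decides.

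The size is a range that rests on assumed correlations. With outcome correlations of 0.3 to 0.7 and time correlations of 0.5 to 0.8, at least one false two-sided rejection occurs in about 13% to 17% of null trials. The ceiling is 18.5%, and the figure is about 9% if all correlations are 0.9. From that upper correlation setting to independence, false claims for active stimulation run at about 6.4% to 9.6% with two-sided p-values, or about 12% to 19% if the tests are one-sided at 0.05.

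The power statement is incomplete rather than shown to be wrong. It belongs to one unnamed test, and without the effect size and variance it can be neither confirmed nor refuted.

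**What to change.** Before the stimulation codes are decrypted, replace the and/or rule with one that holds 5% overall, and state whether the tests are one- or two-sided. Any of these would do:

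- **Max-statistic adjustment.** Within the permutation already planned, compute all four standardised statistics for each permuted assignment and use their maximum (Westfall-Young step-down). This uses the actual correlations, so none need be assumed.
- **Fixed testing order** of the four comparisons, each at 0.05, stopping at the first that fails.
- **One named primary comparison**, with the other three secondary.

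State the same rule in the Abstract and in the Statistical analysis section. In the Sample size section, say which outcome, time point and alpha the 85% refers to. Restate the power only if the chosen rule changes the alpha of that test. Under a fixed order or a single primary comparison it does not, provided the 85% was calculated for the leading test.

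The cost is a wording change and, for the first option, a few lines of code. No new data are needed.

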## Introduction

### Prior research

#### Behavioral therapies

Throughout the progression of primary progressive aphasia (PPA), research supports the use of behavioral interventions targeting two complementary goals: (1) reducing impairments through restitutive therapies^1^ enhancing communication, and (2) increasing daily life participation^2^ through more compensatory approaches (Robinaugh and Henry, 2022; Taylor-Rubin et al., 2021). Restitutive therapies aim to restore lost functions and are typically adapted from well-established therapies for stroke-induced aphasia that target language skills, such as word finding, comprehension, and sentence production. Compensatory approaches focus on supporting individuals in finding alternative ways to accomplish tasks and enhance their active participation despite communication impairments.

Although therapies for PPA resemble those for stroke-induced aphasia, outcomes must be interpreted in light of progressive decline. Unlike stroke-induced aphasia, which results from a sudden, delimited brain injury and exhibits spontaneous recovery, PPA presents distinct challenges with its progressive language decline due to more diffuse neurodegeneration, even when receiving therapy (Norise and Hamilton, 2016). Therefore, a necessary consideration when measuring therapy efficacy in individuals with PPA is the expected gradual decline in abilities throughout the intervention period. Still, it remains crucial to assess the retention of skills present at baseline and the learning of newly acquired skills after the end of therapy (maintenance) and their generalization to other target words and language abilities (Cotelli et al., 2020). These measures are essential for understanding the functional significance of a given therapy and its impact on participants' daily communication. See Cotelli et al. (2020), Beales et al. (2018), and Cadorio et al. (2017) for reviews on maintenance and generalization following naming treatments with individuals living with PPA.

A recent systematic review identified 103 studies that reported behavioral treatments for individuals living with PPA (Wauters et al., 2023). Many studies were focused on restitutive therapies targeting anomia and agraphia since these are among the most common deficits in all variants. Anomia, for example, is a symptom encountered in all PPA variants. However, it may be caused by a breakdown at different levels of the naming process (e.g., at the conceptual level in individuals with semantic variant PPA (svPPA) and the lexical access level in individuals with logopenic PPA (lvPPA). Few studies included in the review investigated restitutive therapy targeting other areas of language and communication, such as semantic knowledge, phonology, speech production and fluency, syntax and morphology, word comprehension, spoken discourse production, or general language and cognition, and compensatory therapies such as augmentative and alternative communication and more functional communication strategies (Wauters et al., 2023).

Restitutive therapies targeting anomia in individuals living with PPA have yielded encouraging results immediately following intervention for trained items and generalization to untrained items, as well as leading to maintenance of therapy gains several weeks after therapy. Indeed, reviews supporting the benefits of spoken naming therapies have been published in recent years (Robinaugh and Henry, 2022; Taylor-Rubin et al., 2021; Wauters et al., 2023; Volkmer et al., 2020). Various approaches have been documented with individuals living with PPA, including semantic therapies emphasizing the meaning of the target words and phonological/orthographic therapies involving sound or spelling cues for the target words, for both nouns and verbs (Robinaugh and Henry, 2022; Taylor-Rubin et al., 2021; Wauters et al., 2023; Volkmer et al., 2020). These therapies enhance semantic or phonological activation to support word retrieval, following psycholinguistic models like the restricted interaction account (Goldrick and Rapp, 2002). Although maintenance and generalization are not measured in all studies, most of the high-quality studies identified in the review by Wauters et al. (2023) documented at least one participant exhibiting generalization and maintenance of treatment gains. The magnitude of therapy effects in these studies was small, as could be expected given the context of a neurodegenerative disorder.

Furthermore, restitutive behavioral therapies targeting agraphia in individuals living with PPA have also shown positive results as reported by recent reviews (Taylor-Rubin et al., 2021; Wauters et al., 2023), and more specifically, work done by our team (Rapp and Glucroft, 2009; Tsapkini and Hillis, 2013; Tsapkini et al., 2014, 2018). In an initial study, Tsapkini et al. (2014) implemented an intervention targeting the relearning of phoneme-to-grapheme conversion (PGC, also known as sound-to-letter correspondence), a skill that is often impaired in individuals with PPA. This intervention yielded gains for the trained phoneme-grapheme pairs (Tsapkini et al., 2014). In a subsequent trial, Tsapkini et al. (2018) applied the “spell-study-spell” therapy, representing a “lexical” therapy focusing on training the spelling of entire words (Rapp and Glucroft, 2009). Again, therapy led to improvements in spelling for the trained words; however, there was no generalization to untrained words when therapy was given alone (Tsapkini et al., 2018).

#### Neuromodulation

Neuromodulation methods, like tDCS, have attracted significant interest over the past decade as promising adjunctive interventions for individuals living with PPA. As recent studies and meta-analyses of combined behavior and neuromodulation interventions in individuals with PPA have shown, a great strength of these approaches (and tDCS in particular) is the increased maintenance and generalization effects compared to behavioral therapy alone, at least in spoken naming and spelling (Cotelli et al., 2020; Coemans et al., 2021; Wang et al., 2023; Nissim et al., 2020). tDCS involves safe, non-invasive application of electrical currents to modulate neuronal activity in targeted brain regions, enhancing neural plasticity (Norise and Hamilton, 2016; Rahman et al., 2013; Sebastian et al., 2016; Stagg and Nitsche, 2011) and potentially aiding language recovery in individuals with PPA by modulating cortical excitability (Ficek et al., 2018; Meinzer et al., 2015; Tao et al., 2021).

tDCS is thought to modulate neural activity by altering cortical excitability and neurotransmitter concentrations, particularly by subthreshold modulation of neuronal membranes (Stagg and Nitsche, 2011). In PPA, tDCS has been shown to modulate functional connectivity (FC), which can serve as an indirect correlate of cortical excitability. In a similar crossover, double-blinded, sham-controlled trial preceding the present one, members of our team found that a-tDCS reduced hyperconnectivity between the stimulated left IFG and functionally connected areas more than sham-tDCS, both paired with the same oral and written naming therapy. Furthermore, these reductions correlated with improved language outcomes up to 2 months post-treatment (Ficek et al., 2018; Tao et al., 2021). These decreases usually reflect increased task efficiency as behavior becomes more automated and have been linked to better treatment outcomes (Meinzer et al., 2015). Notably, both reductions and increases in FC have been observed depending on baseline connectivity patterns, suggesting that tDCS may normalize by downregulating or upregulating either hyper- or hypoconnectivity, respectively, depending on the baseline, to support language recovery (Tao et al., 2023). Additionally, reductions in the inhibitory neurotransmitter GABA following tDCS have also been linked to behavioral gains in individuals with PPA (Harris A. D. et al., 2019). Emerging evidence points to variant-specific changes in FC and metabolic alterations induced by tDCS, as measured by FDG PET, extending mechanistic understanding of how tDCS supports recovery in PPA (Tao et al., 2023; Roncero et al., 2023).

Compared to other neuromodulation methods, such as transcranial magnetic stimulation (TMS), tDCS is significantly low-cost and easily portable, making it attractive to implement in home-based therapies (Tippett et al., 2024; Im et al., 2019; Cappon et al., 2024), a feasible and efficacious approach in individuals with PPA, in particular (Neophytou et al., 2024). The simultaneous use of tDCS with behavioral language therapies aligns with the current understanding of neuromodulation mechanisms: the effects of stimulation on cortical reorganization appear to be influenced by the individual's state or current effort, with behavioral activity during or near the time of stimulation directly impacting outcomes (Silvanto et al., 2008; Gill et al., 2015). Research suggests that maximum benefits from stimulation are obtained when the brain area is actively engaged in a relevant behavioral task during or near the time of stimulation (Bikson and Rahman, 2013). The specificity of tDCS has also been demonstrated in PPA, as generalization of tDCS effects occurred only for functions related to the stimulated area (Wang et al., 2023).

Different PPA variants are associated with distinct patterns of neurodegeneration that affect language processing. For example, individuals living with lvPPA typically show predominant left posterior perisylvian or parietal atrophy, while the neurodegeneration in individuals living with non-fluent variant PPA (nfvPPA) is marked by predominant left posterior fronto-insular atrophy (Gorno-Tempini et al., 2011). These regions are critically involved in phonological working memory, syntactic processing, and motor speech planning. Individuals living with svPPA display distinct predominant anterior temporal lobe atrophy and semantic impairments (Gorno-Tempini et al., 2011). This study focuses on lvPPA and nfvPPA, where stimulation of the left inferior frontal gyrus (IFG) is theoretically and anatomically relevant. Given the importance of the left IFG across various language functions, this area has become a key target for neuromodulation in tDCS studies aimed at enhancing language outcomes in PPA (Cotelli et al., 2020; Nissim et al., 2020).

For over 10 years, the research teams involved in this multisite study have investigated the potential of tDCS as a catalyst for therapeutic interventions. In the same studies discussed previously, Tsapkini et al. (2014, 2018) investigated the effectiveness of tDCS paired with speech-language treatment in individuals with PPA through randomized, double-blind, sham-controlled, within-subject crossover designs. In these studies, anodal-tDCS (a-tDCS) was applied over the left IFG simultaneously with the written naming/spelling therapies (Tsapkini et al., 2014; 2018). These studies produced positive outcomes with a-tDCS combined with behavioral therapy, yielding over 15% more improvement than behavioral therapy paired with sham-tDCS (s-tDCS) for individuals with PPA, albeit at different degrees for each variant. Significantly, a-tDCS promoted the generalization of treatment effects to untrained items and beyond the targeted tasks to functions subserved by the stimulated area (Tsapkini et al., 2018; Wang et al., 2023). Studies by Roncero et al. (2017, 2019) have found similar results following left inferior parieto-temporal stimulation combined with spoken naming therapy: a-tDCS, when combined with behavioral therapy, led to over 20% more improvement than s-tDCS both paired with the same behavioral therapy, and to the generalization of treatment effects to untrained items. Other research groups have also reported that a-tDCS interventions lead to greater maintenance of gains over time compared to behavioral therapies alone, highlighting the potential of this non-invasive neuromodulation technique as an adjunct to behavioral therapies in the management of PPA. As research in this area continues to evolve, tDCS offers new possibilities for improving language outcomes and quality of life in individuals living with PPA (Cotelli et al., 2020; Coemans et al., 2021; Nissim et al., 2020; Sebastian et al., 2016; Byeon, 2020).

Predicting therapy outcomes in individuals living with PPA remains a complex endeavor, with numerous factors influencing treatment response. Factors such as the PPA variant have been shown to influence therapy response. For example, it was found that those with non-fluent variant PPA (nfvPPA) tend to benefit more from tDCS (i.e., improve in both trained and untrained material) (Tsapkini et al., 2018). Moreover, individuals living with either nfvPPA or lvPPA have shown good therapy response and generalization (Tsapkini et al., 2018), contrasting with individuals with svPPA for whom comprehension deficits could limit generalization (Tsapkini et al., 2018; Rogalski et al., 2011), though they are still able to learn (Tsapkini et al., 2018; Hung et al., 2017). Despite strides in identifying a variety of predictors, including structural imaging (brain region volumes and cortical thickness) (de Aguiar et al., 2020a; Nissim et al., 2022), white-matter integrity (Zhao et al., 2021), functional connectivity (Wang D. et al., 2024), baseline language and cognitive abilities (de Aguiar et al., 2020b; McConathey et al., 2017), demographic (e.g., sex; see Licata, Zhao (Licata et al., 2023) and lifestyle factors (e.g., sleep (Herrmann et al., 2022), gaps persist in predicting therapy outcomes and tDCS responsiveness. It is not fully understood which factors predict the effectiveness of tDCS more than others. In this regard, genetic factors also appear to play a significant role.

